### Ethical considerations

The Norwegian Regional Ethical Committee have approved the study (2012/2265/REK sør-øst C). The research will be carried out in compliance with the Helsinki Declaration. Personal confidentiality is guaranteed, and each participant, having received detailed information on the study processes and purposes and affirming their right to withdraw from the study at any time without any explanation, will sign a declaration of voluntary participation. No participant will receive an intervention that is below the current standard of care, since participants in the control group will receive standard HOA care, whereas participants in the intervention group will receive an occupational therapy intervention as a supplement to standard HOA care.

### Confidentiality

All data collected will be regarded as confidential and will be securely stored in paper formats in a locked closet in a locked room. The project leader shall regularly remain in touch with the local project leaders and provide assistance in the data collection process, in addition to ensuring that the data are collected, stored and quality assured in accordance with current guidelines.

### Intervention providers

Six occupational therapists (two at each centre) with at least 4 years of experience within rheumatology will provide the occupational therapy intervention. Before the start of the inclusion process, the therapists will meet together with the project leader and the patient research partner and go through assessment and treatment procedures to ensure that these are performed and delivered consistently. Meetings will be held regularly throughout the trial period. Additionally, the project leader will answer therapists’ questions by mail or telephone between meetings.

### Treatment interventions

Both groups will receive medical treatment as usual.

#### The control group

Participants in the control group will receive information about hand osteoarthritis.

#### The occupational therapy intervention

Based on international recommendations for HOA care and the previous research described above, the occupational therapy intervention will comprise patient education, hand exercises, provision of assistive devices and provision of orthoses. All participants in the intervention group will also receive a treatment diary containing written information about the elements in the intervention and pages for documenting exercises and their use of orthoses (see Table 1).

**Table 1 Tab1:** Treatment diary

Pages	Content
4	Information about hand osteoarthritis.
5–7	Information about ergonomic principles and use of assistive devices, illustrated with photos of ergonomic techniques and the use of the five assistive devices provided as part of the occupational therapy intervention.
8	Information about the rationale for using orthoses, with pictures of the day and night ortohoses.
9	Pictures of activities performed with the day orthosis.
10	Information about the rationale for hand exercising, and general advice regarding how to design an exercise plan, the importance of sitting comfortably, remembering to breathe and to keep the shoulders low while performing the hand exercises, and instructions for the warm-up period. Information regarding the weekly frequency, number of repetitions and intensity of each exercise, and how to adjust the programme in the exercise period.
11	Exercise plan, in which participants will be encouraged to write down when (day and time) they will exercise.
12–13	The exercise programme.
14–17	Four pages (one for each week), each containing • three sections with an 11-point numeric rating scale in which the participants will report date and length of exercise session, rate their pain immediately after exercising (0 = no pain and 10 = maximum pain), and give comments (including registration of adverse events) • one section with each day of the week where participants will record days and nights with using orthosis and length of use (day and night) in hours and minutes
18	A text stating that “you have now finished 1/3 of the programme”, together with a cartoon and an exercise plan which the participant may use if she/he needs to revise her/his original plan.
19–22	Four more pages (one for each week) for recording of hand exercising, pain immediately after exercising, and the use of day and night orthoses.
23	A text stating that “you have now finished 2/3 of the programme”, together with a cartoon and an exercise plan which the participant may use if she/he needs to revise her/his original plan.
24–27	Four more pages (one for each week) for documenting hand exercises, pain immediately after exercising, and the use of day and night orthoses.
28	A last page with a text encouraging the participant to continue exercising two to three times a week, and a reminder that they must bring the treatment diary to the next occupational therapy appointment.

The patient education will comprise information about hand osteoarthritis, ergonomic principles and the use of five assistive devices that the participants will receive during the first consultation. These will be the five devices most frequently used by participants in an RCT evaluating the effect of assistive devices in HOA [33]; a bread knife and a vegetable knife with build-up handles, an enlarged grip for opening bottles, a key for opening jars (the Jar Key), and a self-opening pair of scissors.

The hand exercise programme will be based on the programme used in one of the previously described Norwegian studies [38], and contains seven exercises to prevent or delay development of fixed deformities, and to maintain or increase the range of motion, grip strength and joint stability in the wrist and finger joints (see Table 2). The programme will follow the American College of Sports Medicine’s recommendations regarding exercise intensity, session frequency and length of exercise period [55].

**Table 2 Tab2:**
[figure not shown]
The hand exercise program

All participants will also receive a day and a night orthosis (Table 3). The design of the day orthosis will depend on the degree of CMC-OA, deformity and sub-luxation of the thumb, but the first choice will be the Push Brace^TM^ orthosis. This is a small, water resistant, rigid, pre-fabricated orthosis supporting the CMC1-joint while allowing optimal mobility of the wrist and fingers. The orthosis will be fitted to the participant according to sizing instructions provided by the manufacturer. Alternative day orthoses will be the Camp 28558 thumb orthosis with Orfit Classic 2 mm-Micro, (art.no. 8333. SO2.), inserted around the CMC1 and MCP1 joint to provide extra support, or a custom made CMC1 orthosis made in Orfit Classic 2 mm-Micro, (art.no. 8333.SO2.), to support the CMC1 and, if necessary, also the MCP1- joint.

**Table 3 Tab3:**
[figure not shown]
Orthoses provided to participants in the intervention group

The night orthosis will be designed to prevent thumb subluxation and adduction. It is custom made in Orfit Classic 2 mm-Maxi (art. no. 8333.SO3), and lined with Velour Cotton, (art. no. 5004 from Catell).

Participants will be encouraged to use the orthoses as much as possible, both during daytime (day orthosis) and nighttime (night orthosis).

### Treatment adherence

Participants in the intervention group will document exercises and the use of orthoses in a treatment diary (see Table 1). The diary will have one page for each week in the 3-month treatment period. Each of these pages contains three sections in which the participants will report date and length of the individual exercise session, rate their pain immediately after exercising on an 11-point numeric rating scale (0 = no pain), and provide comments. On each page, there is also one section listing each day of the week where participants will record days and nights on which they used the orthosis, the length of use in hours and minutes, and add any comments they may have.

### Outcome measures

The primary outcome will be the number of participants in each group who have received surgical treatment after 2 years.

Secondary and tertiary study outcomes are documented in Table 4 and are based on previously validated measures.

**Table 4 Tab4:** Secondary and tertiary outcome measures

	Data collection instrument and scale	Time points
Secondary outcome measures:		
Activity performance	MAP-Hand, mean of 18 standardized and up to five patient specific activities, respectively, rating scale 1–4, 1 is no problems	t1, t2*, t3, t4, t5
Physical function and symptoms in the arm, shoulder and hand	Quick-Dash, sum-score range 1–100, 1 = good function	t1, t3, t4, t5
Current situation with regards to main reason for wanting surgery	Numeric rating scale: 0–10, 0 is as bad as could be	t1, t3, t4, t5
Pain at rest	Numeric rating scale: 0–10, 0 is no pain. Both hands.	t1, t3, t4, t5
Grip strength	In Newton by the Grippit; maximum, mean and last of 20 recordings over a 10 s interval, both hands	t1, t3, t4, t5
Pain following measure of grip strength	Numeric rating scale: 0–10, 0 is no pain, both hands	t1, t3, t4, t5
Tertiary outcomes:		
Current pain in thumb selected for surgery	Numeric rating scale: 0–10, 0 is no pain	t1, t3, t4, t5
Painful finger joints	Examination by a trained OT of presence of pain yes/no in CMC1, MCP, PIP and DIP-joints in both hands	t1, t3, t4, t5
Finger flexion	Flexion deficit in millimetre of the II, III, IV and V finger of both hands	t1, t3, t4, t5
Range of motion thumb MCP	In degrees by a goniometer, both hands	t1, t3, t4, t5
Range of motion thumb IP	In degrees by a goniometer, both hands	t1, t3, t4, t5
Palmar abduction thumb	In degrees by a pollexograph, both hands	t1, t3, t4, t5
Abduction CMC1	In degrees by a pollexograph, both hands	t1, t3, t4, t5
Pinch strength	In Newton by the Grippit; maximum, mean and last of 20 recordings over a 10 s interval, both hands	t1, t3, t4, t5
Pain following measure of pinch strength	Numeric rating scale: 0–10, 0 is no pain, both hands	t1, t3, t4, t5
Pain following exercising	Exercise diary, numeric rating scale: 0–10, 0 is no pain	t3
Satisfaction with HOA care at current centre	Numeric rating scale: 0–10, 0 is very dissatisfied	t3, t4, t5

t1 = baseline, t2* = two weeks after baseline (control group only), t3 = 4 months after baseline, t4 = 18 months after baseline, t5 = 24 months after baseline. *CMC1* Carpometacarpal joint of the thumb, *MCP* Metacarpal joint, *PIP* Proximal interphalangeal, *DIP* Distal interphalangeal, *IP* Interphalangeal, *HOA* Hand osteoarthritis, *OT* Occupational therapist

Patient-reported outcome measures will be collected at baseline, 4, 18 and 24 months and will include the following symptoms, functional aspects and measures: Activity performance measured by the MAP-Hand [52, 53]; physical function and symptoms in the arm, shoulder and hand measured by the Quick-Dash [56]; current situation for main reason for wanting CMC1-surgery on a 0–10 numeric rating scale; pain at rest and pain following measures of grip and pinch strength in right and left hand, respectively, on 0–10 numeric rating scales; satisfaction with care for HOA at current centre on a 0–10 numeric rating scale; comfort with use of assistive devices reported on a 0–10 numeric rating scale; and health-related quality of life using the EuroQol EQ-5D [57]. Participants in the control group will also complete the MAP-Hand in a telephone interview 2 weeks after baseline assessments. At the time of rescoring, perceived change in disease activity will be recorded on a global rating scale by asking participants to compare their current status with how they felt 2 weeks ago and mark on a five-point scale whether the disease has become much worse, slightly worse, unchanged, slightly better, or much better.

Additionally, the following observer-reported outcome measures will be reported at baseline, 4, 18 and 24 months: number of painful joints in each hand; joint mobility of digits 2–5 recorded as flexion deficit in mm for each finger [58]; range of motion of thumb metacarpophalangeal and interphalangeal joints measured by a goniometer; CMC1 and palmar abduction of the thumb measured with the Pollexograph [59]; and grip and pinch strength measured in Newton by the Grippit electronic instrument [60]. The therapists will also document the time spent to provide the occupational therapy intervention at baseline, 2 weeks (intervention group only), 4, 18 and 24 months.

Further, the direct and indirect costs in the study period will be self-reported at 4, 18 and 24 months as the number of days of sick leave and absence from paid work, number of visits to a given list of health providers and the number of hospital visits or stays over the period since previous control (see table 5). All participants will also report on any medication taken for their HOA, as well as medical or technical equipment purchased.

**Table 5 Tab5:** Adherence, cost effectiveness and other measures

	Data collection instrument and scale	Time points
Adherence:		
Hand exercises (intervention group only)	Treatment diary, recording of days with exercising, length of exercising in minutes	t3
Orthoses (intervention group only)	Treatment diary, recording of days and nights with using orthosis and length of use (day and night) in hours and minutes	t3
Possession and use of assistive devices	Questionnaire with 20 specified devices with possibility of adding more, possession of each device yes/no, if yes; use regularly, use only when in pain, do not use	t1, t3, t4, t5
Cost-effectiveness:		
Utility	European Quality of Life Scale (EQ-5D), which comprises the EQ-5D index and the EQ-5D visual analogue scale	t1, t3, t4, t5
Treatment sessions	Number and length of each treatment session	t1, t2, t3, t4, t5
Orthoses	Number and type of orthoses	t1, t2, t3, t4, t5
Hand exercises	Number and type of exercise material	t1, t2, t3, t4, t5
Assistive devices	Number and type of device	t1, t2, t3, t4, t5
Sick leave and absence from work	Number of days	t3, t4, t5
Use of medication	Name and dosage of medicine	t1, t3, t4, t5
Health care utilisation	Number of visits and/or hospital stays	t3, t4, t5
Medical or technical equipment	Type and costs of equipment purchased	t3, t4, t5
Other measures		
Age	Years	t1
Gender	Female/male	t1
Marital status	Living alone or not	t1
Employment status	Working full time/ working part time/ not working/ student/ working full time in the home/ unemployed or seeking work /age retired/ disability pension/ sick leave	t1
Level of education	7–10 years of education, 10–12 years of education, 13–15 years of education, more than 15 years of education	t1
Hand dominance	Right or left	t1
Other diseases/previous injuries that may negatively impact hand function	Yes/no, if yes-what kind of disease/injury	t1
Previous hand surgery	Yes/no, if yes-right hand, left hand or both hands	t1
Referred for surgery in	Right hand, left hand or both hands	t1
Main reason for wanting surgery	Description of the main reason	t1
Previously received hand therapy due to HOA	Yes/no, if yes-what kind of therapy	t1
Motivation for surgery	Numeric rating scale: 0–10, 0 is no motivation	t1
Joints with osteoarthritis (as diagnosed by physician or finger joints with bony enlargement)	Marked by the OT on a map with joints of the body	t1
Degree of CMC1-HOA	Conventional radiography of both hands, graded according to the Kellgren-Lawrence method, with grades from 0 to 4, (grade 4 indicating large osteophytes, severe sclerosis and narrowing joint space)	
Degree of radial trapeziometacarpal subluxation	Conventional radiography of both hands, graded as subluxation ratio using a digital calculation calliper	
Presence of erosive HOA	Conventional radiography of both hands, ≥1 joint with erosion = erosive OA.	
Comorbidity	Presence of 16 diseases/health problems (yes/no)	t1
Comfort with use of assistive devices	Numeric rating scale: 0–10, 0 is very uncomfortable	t1, t3, t4, t5

t1 = baseline, t2* = two weeks after baseline (control group only), t3 = 4 months after baseline, t4 = 18 months after baseline, t5 = 24 months after baseline, *CMC1* Carpometacarpal joint of the thumb, *HOA* Hand osteoarthritis

Participants in the intervention group will report treatment adherence in the treatment period between baseline and 4 months in a treatment diary (see Tables 1 and 5).

To be able to describe and compare participants, we will, at baseline, record the participants’ age, gender, marital status, employment status, level of education, hand dominance, other diseases or previous injuries that may negatively impact hand function, previous hand surgery, in which hand they are referred for surgery, previous hand therapy, main reason for wanting surgery, motivation for surgery, current medication taken for HOA, and joints with osteoarthritis (including interphalangeal joints with bony enlargement in each hand). The degree of CMC1-OA and trapeziometacarpal subluxation and the presence of erosive HOA will be evaluated based on radiographs taken in relation to referral to surgical evaluation (Table 5) [61].

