### Functional assessment of hand osteoarthritis

Appropriate outcome measures, based on patients’ concerns, are necessary for the comprehensive evaluation of existing and new interventions in HOA [48]. Such instruments should also be feasible, valid, reliable, and responsive to change. Currently, two patient reported outcomes (PROs) have been developed specifically for HOA: the Australian/Canadian Hand Osteoarthritis Index (AUSCAN) [49] and the Functional Index of HOA (FIHOA) [50]. In a Norwegian study comparing the psychometric properties of these measures, the results indicated that both of these questionnaires contained items that were deemed irrelevant by the Norwegian respondents, such as gender-specific questions and items addressing activities that are not relevant in a Norwegian context [51]. The items are further limited to activities within self-care and house work, and do not include any questions related to activities within work or leisure. The Measure of Activity Performance of the Hand (MAP-Hand) is a PRO where the items were generated through interviews with people with arthritis [52]. In addition to 18 standardized items, the questionnaire includes five open questions, where patients can add other activities of importance to daily functioning. This provides clinicians with important information for goal-setting processes, planning and evaluation of interventions, and meet the need for outcome measures that incorporate the patient perspective as stated by the Outcome Measures in Rheumatology Group (OMERACT) [48]. MAP-Hand has been tested for validity and responsiveness in rheumatoid arthritis (RA) and HOA with good results, but studies of reliability, including estimating the smallest detectable difference and minimal important change are warranted [53].

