### Participants

All persons who are referred by their GP for surgical consultation due to their CMC1-OA at one of the three participating departments of rheumatology are eligible for the RCT. However, persons who do not speak the Norwegian language will be excluded, as will those with cognitive dysfunction or with other diseases or injuries that may negatively impact hand function. The local project coordinator at each centre will have access to lists of patients who are referred for surgical consultation and will mail written information about the study to potential participants. The local project coordinator will telephone those who agree to participate and will book them for the next convenient appointment for the baseline assessment, which is expected to last approximately one hour. A questionnaire will be sent to the participant, who will be encouraged to fill it out and bring it to the appointment. On arrival at the centre, the local project coordinator will screen the potential participant for eligibility before discussing the study with participants and obtaining their written informed consent prior to further assessment and randomization.

Those who do not respond to the mailed written information or who fail to appear at the appointment for baseline assessment will not be re-contacted regarding participation in the study.

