### Data collection

Participant flow is shown in Fig. 1. Follow-up will be at 4 months (immediately before the surgical consultation), 18 months and 24 months after randomization to evaluate short, medium and long-term effects. Before each follow-up, a questionnaire will be sent to the participants, who will be asked to fill it in at home and bring it to the follow-up appointment.

Additionally, participants in the control group will receive a phone call 2 weeks after baseline assessments, and will complete the MAP-Hand in a telephone interview. Participants in the intervention group will be convened for a second consultation 2 weeks after baseline, at which time the orthoses and the hand exercise programme will be adjusted, and additional information regarding use of assistive devices will be given if needed.

The surgical consultation takes place immediately after the follow-up assessment at 4 months. Based on the patient’s symptoms, functional limitations and degree of CMC1-OA, the surgeon may reach one of the three following conclusions;the patient is not eligible for surgery, and will need a new referral from his/her GP to be scheduled for a new surgical consultationthe patient is scheduled for a new surgical consultation after 6 to 12 months, due to uncertainty related to eligibility, orthe patient is eligible for surgery and will receive an appointment for operation, (usually after 6 to 10 months on a waiting list).

All participants who are operated on, regardless of group affiliation, will be given post-operative treatment according to surgical procedures and recommendations.

The third and fourth follow-up will be after 18 and 24 months, respectively. Baseline assessments will be repeated, and for participants in the occupational therapy group, exercises and orthoses will be adjusted if needed. Participants in the control group will receive the occupational therapy intervention after assessments at the control at 24 months.

Each participant will have a special numeric code, and all data will be stored in a fireproof and locked cupboard and in a digital file on the research server at Diakonhjemmet Hospital. Selected members of the project group (project leader, local coordinators, bio-statistician, study assistants, a PhD-student and a post doc research fellow) can access the file. The OT will check missing data in the questionnaires at each follow-up. An independent study assistant will check incorrect and double data entries.

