### Statistical analyses

The main treatment analysis will be conducted blinded to treatment allocation and will be analysed on an intention-to-treat basis with all randomized participants retaining their original randomized group. In the analysis of the primary outcome, the number of participants in each group who have received surgical treatment after 2 years will be compared using binary mixed models logistic regression and presented as odds ratios with a 95% CI.

We will also use mixed Cox proportional hazard models to describe and compare time to operation in the two groups, including establishment of the vital assumption of proportionality of the hazard rates.

In terms of secondary and tertiary outcomes, differences in mean values with 95% CI at each follow up will be analysed using mixed models analysis of covariance, adjusting for baseline levels of the outcome measure, while generalized linear mixed models will be used to estimate the overall effect for the total 2-year trial period, adjusting for the effect of clustering and repeated measures over time.

The assessment of the psychometric properties of MAP-Hand (research question 4) will adhere to the methods recommended by the international COSMIN group, using Kappa and ICC for examining test-retest reliability, and an anchor-based approach (based on the five-point global rating scale) to determine the minimal important change [62]. The smallest detectable change will be assessed by examining limits of agreement of repeated measures, computed as ± 1.96 SD of the difference between baseline scores and retest scores. The results from participants who report change in disease activity between baseline and rescoring will be excluded from the analysis of test-retest reliability and the smallest detectable change.

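### The MAP-Hand retest is by telephone while the baseline form appears to be self-completed, so the planned statistics estimate between-mode agreement, not test-retest reliability of the form

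*Protocol article*

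**What the plan says.** Under Functional assessment of hand osteoarthritis, the protocol article describes the MAP-Hand as a patient-reported outcome: "In addition to 18 standardized items, the questionnaire includes five open questions". Under Participants, it describes what happens before the baseline visit: "A questionnaire will be sent to the participant, who will be encouraged to fill it out and bring it to the appointment".

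The retest is described twice, consistently. Data collection says that control participants "will complete the MAP-Hand in a telephone interview" two weeks after baseline. Outcome measures says: "Participants in the control group will also complete the MAP-Hand in a telephone interview 2 weeks after baseline assessments". Table 4 likewise lists the two-week MAP-Hand for the control group only.

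For the later visits, Data collection says that a questionnaire is sent to participants, "who will be asked to fill it in at home and bring it to the follow-up appointment".

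Under Statistical analyses, reliability is assessed "using Kappa and ICC for examining test-retest reliability", and the smallest detectable change comes from limits of agreement "computed as ± 1.96 SD of the difference between baseline scores and retest scores". Participants who report changed disease activity are left out of these analyses. The article mentions no same-mode retest, no check that the two modes are equivalent and no caveat about mode.

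**The concern.** Test-retest reliability asks how far scores differ when the same instrument is given twice, under the same conditions, to people who have not changed. Here the conditions appear to differ for everyone: form first, interviewer second. People may answer a caller differently from the way they answer a form, and such a difference enters the baseline-to-retest comparison alongside ordinary measurement error.

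Excluding participants who report change removes true change but does nothing about mode. A later analysis plan cannot repair the problem either, because the confounding is built into data collection.

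What is at stake is the answer to research question 4, for which the article plans a separate publication, and the smallest detectable change that comes from it. The trial's own MAP-Hand changes run from questionnaire to questionnaire, so an error estimate from a questionnaire-telephone pair does not directly apply to them.

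**Working it through.** The article states no ICC, kappa, smallest detectable change or mode effect, so there is no figure of its own to reproduce. The check has three steps: what the passages fix, what the algebra implies, and how large the effect could be under stated assumptions.

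**1. Mode at each occasion**

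| Occasion | Mode | Source |
|---|---|---|
| Baseline | Self-completed form (inferred) | Functional assessment; Participants; Outcome measures |
| 2 weeks, control group | Telephone interview (stated) | Data collection; Outcome measures |
| 4, 18 and 24 months | Questionnaire filled in at home (stated) | Data collection |

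On this reading every test has one mode and every retest the other. No participant contributes a same-mode pair, so the data cannot separate mode from error.

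**2. Algebra**

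Write test = T + e1 and retest = T + m + u + e2. Here m is a mode shift common to everyone, and u is person-to-person variation in the mode effect, with SD su. The error SD is se on both occasions, and the true-score SD is st. The total variances are v1 = st² + se² and v2 = v1 + su².

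- Planned smallest detectable change = 1.96 × sqrt(2se² + su²). The common shift m does not appear.
- Consistency ICC = 2st² / (v1 + v2).
- Agreement ICC = 2st² / (v1 + v2 + m²).

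A common shift therefore lowers only the agreement ICC (and can lower kappa). Variation su lowers both ICC forms and widens the smallest detectable change. The article does not say which ICC form is planned.

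**3. Size, under assumed values**

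*Smallest detectable change.* Assume a same-mode SD of the difference of 0.30 on the 1–4 scale:

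- su = 0: SD = 0.30; 1.96 × 0.30 = 0.588 (no inflation).
- su = 0.15: SD = sqrt(0.09 + 0.0225) = 0.335; × 1.96 = 0.657 (ratio 1.12).
- su = 0.30: SD = sqrt(0.09 + 0.09) = 0.424; × 1.96 = 0.832 (ratio 1.41).

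*ICC, with a second set of assumptions.* Take st = 0.5 and se = 0.2, so v1 = 0.29:

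| m | su | Consistency ICC | Agreement ICC | Planned smallest detectable change |
|---|---|---|---|---|
| 0 | 0 | 0.50/0.58 = 0.862 | 0.862 | 1.96 × sqrt(0.08) = 0.554 |
| 0.3 | 0 | 0.862 | 0.50/0.67 = 0.746 | 0.554 |
| 0 | 0.2 | 0.50/0.62 = 0.806 | 0.806 | 1.96 × sqrt(0.12) = 0.679 |
| 0.3 | 0.2 | 0.806 | 0.50/0.71 = 0.704 | 0.679 |

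The second row shows a shift that harms the agreement ICC and leaves the planned smallest detectable change untouched.

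**The case against.** Several points on the other side have weight.

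- **The baseline mode is inferred.** No sentence says that the MAP-Hand is part of the mailed baseline questionnaire, and completing it beforehand is only encouraged. This limits certainty. A form filled in at the clinic would still be self-completed, however, so the contrast with a telephone interview would remain.
- **The mode effect may be negligible.** Nothing in the article gives its size. The direction is not assured either: an interviewer might reduce skipped or misread items and so lower the retest error. In the first illustration the error variance per occasion is 0.09 / 2 = 0.045. A fall to 0.0225 at retest would exactly offset a mode-effect SD of 0.15, whose variance is 0.0225. This stands, and it is why the size is given as a range starting at no inflation.
- **A call has practical merits.** It fixes the date to which the two-week global rating refers, and a caller could read back the patient's own activities. The fix should keep both advantages.

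Stronger readings are tempting but unsupported. A reader might infer that research question 4 will go unanswered. The question names no mode, and a cross-mode comparison still informs on reliability if labelled as such. A reader might also infer that the smallest detectable change will certainly be too large and that patients with real change will be misclassified. The first depends on an unknown mode effect. As to the second, the article plans no classification of patients by this threshold; trial effects on the MAP-Hand are mean differences with confidence intervals.

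**Conclusion.** The point holds as a limitation of the reliability sub-study. Provided that the baseline MAP-Hand is self-completed, as the article implies, mode and occasion are fully confounded. The planned statistics then estimate between-mode agreement, not the test-retest reliability of the form used at 4, 18 and 24 months.

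The size cannot be known from the documents. The illustrated range for the smallest detectable change, from no inflation to +41%, assumes additive, independent mode variation and equal error in both modes. Its upper end takes person-to-person mode variation as large as the whole same-mode SD of the difference.

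Only research question 4 is touched. The primary surgery outcome does not involve the MAP-Hand, and the between-group MAP-Hand comparisons use the home-completed questionnaire in both arms at each follow-up. The change is worth making because it is cheap and the present design cannot reveal whether a mode effect exists.

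**What to change.** Collect the two-week retest from the control group on the same self-completed MAP-Hand form, together with the global rating item. Carry over the patient-specific activities named at baseline so that the same activities are rated twice. Use the telephone call to prompt completion on the due date, which keeps the two-week reference period of the global rating. Record the completion dates of both forms.

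The cost is postage in place of an interview, and possibly a slightly lower return rate, which the call should partly offset.

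If telephone retests already exist, report them as between-mode agreement, with the mean difference and an agreement-type ICC. Do not present the resulting smallest detectable change as that of the self-completed form. This needs only a change of reporting.
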